# Mechanical hyperinflation maneuver and intracranial compliance of critical neurological patients: protocol for a randomized controlled equivalence trial

**DOI:** 10.1186/s13063-023-07362-5

**Published:** 2023-05-22

**Keywords:** Mechanical ventilators, Stroke, Intracranial pressure, Respiratory mechanics, Physical therapy techniques, Randomized controlled trial, Intracranial compliance

## Abstract

**Background:**

Mechanical hyperinflation maneuver (MHM) is a technique known for optimizing bronchial hygiene and respiratory mechanics; however, its effects on intracranial compliance are not known.

**Methods:**

Sixty patients aged ≥ 18 years, with clinical diagnosis of acute stroke, confirmed by neuroimaging examination, with onset of symptoms within 72 h, under mechanical ventilation through tracheal tube, will participate in this study. Participants will be randomly allocated into 2 groups: experimental group (*n* = 30)—MHM plus tracheal aspiration—and control group (*n* = 30)—tracheal aspiration only. Intracranial compliance will be measured by a non-invasive technique using Brain4care BcMM-R-2000 sensor. This will be the primary outcome. Results will be recorded at 5 times: T0 (start of monitoring), T1 (moment before MHM), T2 (moment after the MHM and before tracheal aspiration), T3 (moment after tracheal aspiration), T4, and T5 (monitoring 10 and 20 min after T3). Secondary outcomes are respiratory mechanics and hemodynamic parameters.

**Discussion:**

This study will be the first clinical trial to examine the effects and safety of MHM on intracranial compliance measured by non-invasive monitoring. Limitation includes the impossibility of blinding the physical therapist who will supervise the interventions. It is expected with this study to demonstrate that MHM can improve respiratory mechanics and hemodynamic parameters and provide a safe intervention with no changes in intracranial compliance in stroke patients.

**Supplementary Information:**

The online version contains supplementary material available at 10.1186/s13063-023-07362-5.

## Introduction

Neurocritical patients with acute neurological impairment, especially stroke, often require the use of mechanical ventilation (MV) [1, 2], either by lowering of the level of consciousness (due to lesion in the thalamus, limbic system, reticular formation in the brainstem), protection of the airways (brainstem), or respiratory control (respiratory center in the cortex, bulb, and pons) [3].

Prolonged MV dependence associated with brain-lung crosstalk and immunosuppression induced by ischemic event [2, 4, 5] can increase the retention of lung secretions and lead to pulmonary complications with an underlying higher risk of death [2].

Evidence corroborates the benefits of using strategies for the removal of secretion associated with MV [6, 7], including MHM, which has been widely applied and discussed [8, 9]. However, hyperinflation causes higher intrathoracic pressure (ITP), which can influence cardiac output (CO), mean arterial pressure (MAP), and intracranial pressure (ICP) [10], thus compromising the indication of this technique. Even though some studies have demonstrated cardiovascular stability during MHM [11, 12], no studies have addressed the monitoring of ICP or intracranial compliance (ICC) during and after the maneuver performance in critical neurological patients. This possibly occurs due to the barrier imposed by the invasive method involving skull trepanning and insertion of a catheter in the cranium, required for monitoring the ICP in traditional methods [13]. Although the technique of inserting a cerebral catheter is the gold standard and most recognized measure for ICP monitoring, the exigence of surgical intervention, training, and specific interpretation technique make it financially unviable for studies at intensive care units (ICUs) on a small and large scale.

Over the past few years, a new instrument has been proposed for non-invasive monitoring of ICC through a sensor capable to detect bone cranial deformation derived from ICP variation [14, 15], which allowed to monitor these patients, called Brain4care (B4C) sensor. The method is in good agreement with the invasive method, the gold standard for the detection of intracranial hypertension [16].

The B4C technology allows analyzing the ICP waveform, composed of the components (peaks) P1, P2, and P3, and the relationship between these different components provides information about the ICC. ICC is characterized by the relationship between the volumes of intracranial components (brain, cerebrospinal fluid, and blood). The loss of hemostasis between these components is related to a substantial increase in ICP [15].

In this context, considering the need to perform MV in critical neurological patients, as well as the retention and need for effective, safe removal of lung secretions and related clinical impact on ICC variation, our objective was to develop an MHM protocol and investigate its effects on ICC and respiratory mechanics on patients with stroke.

## Methods

### Trial design

The protocol complies with a randomized controlled equivalence trial, double-blinded, parallel (1:1 ratio), and exploratory approved by the Research Ethics Committee of the Hospital de Clínicas of the Universidade Federal do Parana (CAAE: 01,378,118.7.0000.0096). The individuals are allocated through simple randomization into two groups. All items in the Data Set of the Register of Tests by the WHO were recorded on the database of the Brazilian Clinical Trial Registry (RBR – 5qs9k2n). Any alteration in the protocol is informed to the above-mentioned bodies. When preparing this protocol, we used the SPIRIT reporting guidelines [17], and a table with the standard protocol items (SPIRIT) is presented in Table 1. The SPIRIT checklist is available as an additional file (Additional file 1).

**Table 1 Tab1:** Time schedule of enrollment, interventions, assessments, and visits for participants according to Recommendations for Interventional Trials (SPIRIT)

		**Study period**						
		**Enrollment**	**Allocation**	**Post-allocation**			**Close-out**	
**Time point**		**-t1**	**T0**	**T1**	**T2**	**T3**	**T4**	**T5**
**Enrollment**								
Eligibility screen		X						
Informed consent		X						
Allocation			X					
**Interventions**								
Control group					X	X		
Experimental group					X	X		
**Outcomes variables**								
**Background information**								
Socio-demographic and clinical characteristics		X						X
**Primary outcome measures**								
Intracranial compliance	Relation P2/P1			X	X	X	X	X
	TTP			X	X	X	X	X
	Pulse amplitude							
**Secondary outcome measures**								
Respiratory mechanics	Static compliance			X	X	X	X	X
	Dynamic compliance			X	X	X	X	X
	Resistance			X	X	X	X	X
	Expired current volume							
Hemodynamic stability	MAP			X	X	X	X	X
	HR			X	X	X	X	X
	SpO_2_			X	X	X	X	X

*TTP* time to peak, *MAP* mean arterial pressure, *HR* heart rate, *SpO*
_*2*_ peripheral oxygen saturation

### Setting and participants

Information and guidelines on this research (objectives, methodology, risks, and benefits) are given to critical neurological patients admitted to ICU at the Clinical Hospital Complex of the Federal University of Paraná and met the inclusion criteria. The term of consent will be obtained by one of the researchers of the group, before the admission of the participant in the research. Their inclusion in the study is effective by agreeing to participate and signing an Informed Consent (IC), according to Resolution 466/2012 by the National Health Council This researcher will make the initial contact with the person responsible for the participant, explaining in detail all the procedures that will be performed.

Individuals with acute stroke diagnosis are included in the study upon neuroimage exam confirmation, with symptoms dating back to 72 h, under MV through a tracheal tube, both male and female and over the age of 18, whose relatives signed the IC. Exclusion criteria included individuals who received contraindication for the enhancement of positive ITP (pneumothorax, hemothorax, and acute respiratory distress syndrome), presented peak pressure (Ppeak) > 40 cmH_2_O in the MV, patients with Richmond Agitation-Sedation Scale (RASS) above -3 (asynchronicity in MV and difficulty in coupling to the ICP monitoring sensor), patients with hemodynamic instability according to higher concentrations of vasoactive amines over the last 12 h, and those who had been subjected decompressive craniectomy.

The following strategies will be carried out for achieving adequate participant: dissemination of the research among members of the multidisciplinary team, training of physiotherapists to screen potential patients for the study, and actively search for patients in intensive care units.

To control possible confusing factors regarding ICP increase, we will assess and monitor the level of carbon gas (CO_2_) exhaled – end-tidal CO_2_ (ETCO_2_) and pain throughout the data collection. ETCO_2_ assessment is performed using a capnograph (*Dräger Vamos@ plus* monitor), whose sensors are calibrated 2 h before the collection period and alarms, reference measures, and oxygen compensation adjusted [2]. Pain is assessed according to the Behavioral Pain Scale, and the evaluation tool focused on behavioral indicators of pain previously translated and adapted to Portuguese [18, 19]. All researchers were properly trained for data collection.

### Randomization and allocation concealment

The participants are randomly allocated to two groups using a simple randomization procedure with computerized random numbers (Randomizer software program—Version 4.0). Participant allocation was conducted using sequentially numbered, opaque and sealed envelopes, opened only at the time of participant’s inclusion in the study. Randomization and allocation procedures were conducted by an independent physical therapist not involved with assessment or interventions, same for recruitment.

### Data management

Prior to the beginning of the trial, study personnel will undergo training sessions on data collection and will be individually tested on data entry as well as outcome assessments. Study data will be collected on a paper form and transferred to an excel spreadsheet. To ensure the integrity of the data, regular quality checks will be performed to assess for missing data and invalid field entries.

All electronic study data will be stored on a secure terminal server at the Department of Prevention and Rehabilitation in Physical Therapy, Universidade Federal do Parana, being access limited only to authorized staff, encrypted and password-protected with limited access. All electronic information will be recorded using study identification numbers, rather than participant names.

All data and all source documents, as well as the consent forms, will be filed archived at in a cabinet with restricted access to members of the research group.

### Interventions

After the assessments, the selected patients are randomly allocated into two groups (Fig. 1): experimental group (EG)—composed of individuals who will be subjected to MHM + tracheal aspiration—and control group (CG)—only tracheal aspiration intervention. All individuals will be positioned on dorsal decubitus at the bedside at 30°; MV is adjusted on assisted ventilation mode, controlling volume, tidal volume (Vt) of 6 ml/Kg of predicted weight, positive expiratory-end pressure (PEEP) 8 cmH_2_O, inspired oxygen fraction (FIO_2)_, peripheral oxygen saturation (SpO_2_) of 94%, and respiratory rate (RR) and flow (V) adjusted to maintain ventilation synchrony and gasometric demands. We will use a number 14 closed aspiration system with verified cuff pressure and the occurrence of leaks. All participants will be subjected to tracheal aspiration, and only 2 h later, the data collection is initiated (Fig. 2). During these 2 h, patients will only be monitored and maintained on the initial position; no concomitant procedures or disconnection of MV circuit are conducted. In case it is not possible to maintain such conditions, the collection is suspended and started again at the appropriate moment. According to Robba et al. (2016), PEEP of 8 does not cause effects on ICP [20].

**Fig. 1 Fig1:**
[figure not shown]
Flowchart of recruitment, interventions, and evaluations of participants. EG, experimental group; CG, control group; Vt, tidal volume; V, flow; RR, respiratory rate; Ti, inspiratory time

**Fig. 2 Fig2:**
[figure not shown]
Schematic drawing of experimental design. T0 to T5 represents the assessment stages. DD, dorsal decubitus; EG, experimental group; MHM, mechanical hyperinflation maneuver; CG, control group

Assessments will range five stages: T0 (monitoring start), T1 (before ventilation maneuver for the intervention or control groups), T2 (end of ventilation maneuver our control), T3 (after tracheal aspiration), and T4/T5 (monitoring after 10 and 20 min of procedure). The five initial minutes are required for the initial collection of hemodynamic, ventilation, and neurological data. After the start of this period is T1 with a 10-min duration, followed by T2 and T3, with a 5-min duration each. The individuals in T1 who constituted the MHM group will have their ventilation parameters altered for 10 min according to the lung hyperinflation maneuver adopted, subsequently returning to the baseline values. During this period, the individuals in the control group will be only monitored. In T2, both groups will be subjected to tracheal aspiration; subsequently, data will be monitored for 5 min. Finally, the individuals of both groups were monitored at T4 and T5, 10 and 20 min after the procedure, respectively, to verify vital data stabilization (Fig. 2).

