In scenarios of normality of ICP and ICC, there is a proportion between the peaks, where P1 > P2. However, in situations of abnormality, there is a change in the morphology of the ICP waveform, with an increase in ICP associated with a low ICC, with P2 > P1. For the TPP variable, the higher the value found, the greater the chance of the peak being P2, which also corresponds to a decrease in the ICC [22, 23].

In this study, the evaluations will be carried out in five (T1–T5) moments:T0: start monitoring, the interval between T0 and T1 is intended to ensure patient stabilization for the start of data collection;T1: capture initial patient data;T2: assess whether the MHM protocol had effects on ICC;T3: verify whether aspiration combined with MHM could lead to different effects on outcomes;T4 and T5: check whether there was stabilization of parameters related to ICC and respiratory mechanics.

The moment of evaluation T2 is the most relevant for the primary outcome; as for the secondary outcomes, evaluations from T2 to T5 are the most relevant.

Data will be collected through a monitor and analyzed using the Brain4care Analytics System, considering that at a time interval, the software selects an average of pulses to form the waves.

To capture the data, the ICP assessment sensor will be chosen according to the cranial circumference (S, M, L, XL) considering as protocol the lowest sensor possible with reading, following the manufacturer’s recommendations. Data collection will start after the coupling procedure and confirmation by the assessor of reading compatible with the acceptable ICP curves.

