### Sample size

During an extensive literature search, no randomized clinical trials were found that investigated the effect of MHM on CHF in post stroke patients. Thus, it was decided to use a study that investigated the effects of a physiotherapy technique on ICP for the sample calculation.

To obtain the sample size needed for this study, we used the combination of statistical software’s R and G-Power 3.1. First, we extracted the intracranial pressure with the techniques performed in the study bellow [28]. From this previous work, we detected that the median value of ICP for the control group was 16.9, and for the intervention group, it is 11.7. Then, we calculated the Cohen-D effect size from the medians using the package ‘rcompanion’ in R [29]. The final step using the GPower is where we estimate with a power of 95% and a confidence level of 95% the minimum sample size for a *T-Student* equivalence test [30]. The total number of subjects is 60, equally distributed in two groups of 30 patients.

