### Statistical methods

The collected data will be organized on a spreadsheet and summarized using techniques of descriptive statistical analysis. The qualitative variables will be summarized by building frequency tables and the quantitative variables by calculating the descriptive measures (average, mean, standard deviation, and percentiles 25–75).

The evaluations’ primary outcome and secondary outcomes will be made in 5 different times; for that, the data will be analyzed by analysis of variance (ANOVA) two-way for repeated measures with the Tukey post-test for results that present normal distribution and homogeneity of variances, verified by the test of Shapiro–Wilk and Average in Levene, respectively.

We will be using the statistical software Statistical Package for the Social Sciences (SPSS) (IBM—version 22) to analyze the collected data. Our research hypotheses will be tested using non-parametric methods. Wilcoxon test with Kruskal–Wallis post-test will also be applied (intergroups). The level of significance established was *p* ≤ 0.05. The evaluation of results and data analysis will be carried out by an independent professional.

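### T0 is listed as a recorded pre-maneuver assessment but has no clear role, and the planned ANOVA adjusts the key T2 comparison for no baseline reading

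*Protocol article*

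**What the plan says.** The sections of the protocol article give different accounts of T0.

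- **Abstract, Methods:** "Results will be recorded at 5 times: T0 (start of monitoring), T1 (moment before MHM"), and the list runs on to T5. That is six labels for five times.
- **Interventions, text under Fig. 2:** T0 is one of five assessment stages, and "The five initial minutes are required for the initial collection of hemodynamic, ventilation, and neurological data". The same paragraph gives T1 a 10-minute duration and has the experimental group's ventilator settings changed during T1.
- **Primary outcome, Intracranial compliance:** the five evaluation moments are T1 to T5. T0 starts monitoring, and "the interval between T0 and T1 is intended to ensure patient stabilization for the start of data collection". T1 captures the initial data, and T2 is the most relevant moment for the primary outcome.
- **Table 1:** allocation is marked at T0, and the outcome marks run from T1 to T5.
- **Statistical methods:** the evaluations "will be made in 5 different times", which are not named. The model is a two-way repeated-measures ANOVA, with non-parametric tests also planned. No baseline covariate is mentioned. The only covariate named anywhere is adherence or withdrawal, in the section on non-adherence and missing data.

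**The concern.** The trial has an equivalence aim and 60 patients, so the width of the between-group interval at T2 largely decides what can be concluded. Patients with acute stroke are likely to differ widely in waveform indices before anything is done to them. A pre-maneuver reading from the same patient is the cheapest way to remove that spread. As written, the plan describes collecting such a reading at T0, gives it no clear use, and adjusts the T2 comparison for neither T0 nor T1.

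The choice of reading also matters. T1 is the designated baseline in the outcome section, but under Fig. 2 the maneuver takes place within T1. On that account a T1 value in the experimental arm would already contain the intervention. T0 does not have this problem in any section.

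**Working it through.** **The plan's own figure.** The only related figure is the sample size: "The total number of subjects is 60, equally distributed in two groups of 30 patients". It comes from medians ("the median value of ICP for the control group was 16.9, and for the intervention group, it is 11.7", a difference of 5.2) with 95% power and 95% confidence. The article gives no standard deviation, effect size or margin, so 60 cannot be rebuilt. Solved backwards with the normal approximation, two-sided: d = (1.960 + 1.645) × √(2/30) = 0.93, hence an SD of about 5.2/0.93 = 5.6. The described calculation is a two-group t-type test, with no mention of repeated readings or baseline adjustment, so it neither supports nor contradicts what follows.

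**Inputs.** The article states no within-patient correlation. Let r be the correlation of T0 with T1 and of T1 with T2, and q that of T0 with T2. Both are assumptions. The variance at T2 is set to 1.

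**Step 1: one baseline against none.** The residual variance after adjusting for T1 is 1 − r².
- r = 0.6: 0.640, a cut of 36%
- r = 0.7: 0.510, a cut of 49%
- r = 0.8: 0.360, a cut of 64%

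If only T0 can be used, the residual is 1 − q². With q = 0.75 that is 0.4375, a cut of 56%.

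**Step 2: T0 added to T1.** The further relative cut is [(q − r²)/(1 − r²)]². With equal correlations (q = r) it becomes [r/(1 + r)]².

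| Assumption | T1 only | T0 and T1 | Further cut |
|---|---|---|---|
| r = q = 0.6 | 0.640 | 0.550 | 14% |
| r = q = 0.7 | 0.510 | 0.424 | 17% |
| r = q = 0.8 | 0.360 | 0.289 | 20% |
| r = 0.8, q = 0.75 | 0.360 | 0.326 | 9% |
| r = 0.8, q = 0.72 | 0.360 | 0.342 | 5% |
| r = 0.8, q = 0.64 (first-order decay) | 0.360 | 0.360 | 0% |

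As r approaches 1 with equal correlations, the cut tends to (1/2)² = 25%. Under first-order decay q = r², and the cut is 0% at every r.

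**Step 3: proportion.** At r = q = 0.8, T1 alone removes 64 points of the unadjusted variance and T0 adds 0.360 − 0.289, about 7 points. The standard error falls by a further 1 − √(0.289/0.360), about 10%.

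**Step 4: cost.** With 60 patients, two arms and one covariate there are 57 residual degrees of freedom. A second covariate leaves 56, a loss of 1/57, about 2%.

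**The case against.** Several objections have force.

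- **A reader might infer that the plan excludes T0 from the analysis.** The documents do not settle that. Statistical methods leaves its five times unnamed, and two sections count T0 among five. What can be shown is an unresolved role and no baseline covariate.
- **Leaving T0 out has a stated reason.** The outcome section makes the T0–T1 interval a stabilization period, so early readings may be less informative. This stands, and the gain from T0 could then be nil. It is softened by the two procedure-free hours before collection and by the requirement that the assessor confirm an acceptable curve first. Entering T0 as its own covariate lets the data give it little weight.
- **A separate T0 value may not exist.** The opening five minutes could simply lead up to the T1 reading. The sensor is described as recording data for later analysis, which makes a T0 value likely to be recoverable, but the article does not say so outright.
- **The ANOVA may already use T1.** If T1 is one of its times, a group-by-time contrast works on change from T1, with variance 2(1 − r). At r = 0.8 that is 0.40, against 0.36 with T1 as a covariate. So part of the baseline information may be used already, and the gains in Step 1 are against an unadjusted comparison at T2.
- **Covariates are often left to an analysis plan.** True, but the article does commit to a method, and the suggestion is an improvement on that method.

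Two further inferences should be resisted. A 20% gain is neither a ceiling nor a best estimate: it needs equal correlations of about 0.8. And leaving T0 out introduces no bias by itself.

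**Conclusion.** The point holds as an optional gain in efficiency together with a contradiction that needs clearing up. T0 is described as a recorded assessment and is the only stage that every section puts before the maneuver, yet the outcome section and Table 1 start at T1 and the ANOVA adjusts for no pre-maneuver reading. Most of the available precision comes from adjusting for one baseline at all, r² of the variance. Adding T0 to T1 brings a further 0% to 25% of the remaining variance across patterns from first-order decay to equal correlations. Typical values would be 9% with 0.8/0.8/0.75, or 14% to 20% with equal correlations of 0.6 to 0.8. All of this rests on assumed correlations. The randomized comparison at T2 is valid without the change, and adjusting for a reading taken wholly before the maneuver cannot bias it. Adjusting for a T1 value that includes maneuver minutes could, because that is a post-treatment value that may absorb part of the effect at T2.

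**What to change.** 1. Reconcile the abstract, the text under Fig. 2, the outcome section and Table 1 on two questions: whether T0 is an assessment or only a run-in, and whether T1 lies wholly before the maneuver. Name the five analysed times in Statistical methods.
2. Make the between-group comparison at T2 baseline-adjusted, with pre-maneuver readings as covariates and not as outcome times. If T1 is wholly pre-maneuver, enter T1 and T0 as two separate covariates. If T1 includes any maneuver minutes, enter T0 alone.
3. If T0 values are kept, mark them in Table 1. If they prove not to be stored and T1 is clean, adjust for T1 alone, which keeps most of the gain.

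The cost is a few sentences, one table column and, for the second covariate, one degree of freedom (about 2%). No extra patient procedure is needed. The choice should be fixed before outcome data are examined by group.

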### Control group

The CG will be positioned in dorsal decubitus at 30° and will undergo initial ventilatory adjustments and tracheal aspiration, the same procedures performed in the EG 2 h before the start of data collection. Between T1 and T2, they will only be monitored, not going through the MHM. In T3, they will be aspirated as well as EG. They will undergo non-invasive ICC monitoring at the same moments as the EG.

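### T1 and T2 are defined inconsistently: some statements put T1 before the maneuver and T2 before aspiration, others put the maneuver in T1 and aspiration in T2

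*Protocol article*

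**What the plan says.** The protocol article describes the time points in two ways.

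**As moments.** The Abstract lists "T1 (moment before MHM), T2 (moment after the MHM and before tracheal aspiration), T3 (moment after tracheal aspiration". The opening sentence under Fig. 2 (Interventions) agrees: "T1 (before ventilation maneuver for the intervention or control groups), T2 (end of ventilation maneuver our control), T3 (after tracheal aspiration". The Control group section places the maneuver period, or plain monitoring for controls, between T1 and T2. The Intracranial compliance section has T1 supply the initial data, T2 show the effect of the MHM, and T3 show the effect of aspiration combined with the MHM.

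**As blocks of time.** The same paragraph under Fig. 2 goes on: "After the start of this period is T1 with a 10-min duration, followed by T2 and T3, with a 5-min duration each". It then says "The individuals in T1 who constituted the MHM group will have their ventilation parameters altered for 10 min", and after that "In T2, both groups will be subjected to tracheal aspiration; subsequently, data will be monitored for 5 min".

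Two further statements do not fit the block description. The Control group section says of the controls: "In T3, they will be aspirated as well as EG". Table 1 marks interventions for both groups at T2 and T3 and none at T1.

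The Intracranial compliance section singles out T2 as the key time for the primary outcome. It also says that the waveform values are built from one-minute pulse averages. It does not say which minutes supply the value for each T.

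**The concern.** A reading before treatment and a reading during treatment are different quantities, yet T1 can be taken as either. T2 can likewise be read as free of aspiration or as containing it. Whoever cuts the continuous sensor recording into T1 and T2 values has to choose, and the text supports both choices.

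Trial design calls this an equivalence trial, and the Abstract hopes to show no change in intracranial compliance. A T1 value recorded during the MHM in one arm only would pull a T1-to-T2 comparison toward that hoped-for result if the MHM has a lasting effect. The Discussion also says that aspiration itself produces a relevant response in the waveform. A T2 value that includes aspiration therefore cannot be attributed to the MHM alone.

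This is not detail that a condensed article leaves to a fuller document. The article states the timing several times, and the statements do not agree.

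**Working it through.** No sample-size or power figure enters this point, so there is no stated figure to reproduce. The check sets the statements side by side and lays the stated durations on a clock.

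**Side by side**

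| Place in the article | MHM relative to T1 and T2 | Aspiration |
|---|---|---|
| Abstract, Methods | between T1 and T2 | after T2, before T3 |
| Under Fig. 2, opening sentence | T1 before it, T2 at its end | before T3 |
| Under Fig. 2, later sentences | inside T1 | inside T2 |
| Control group | between T1 and T2 | in T3, both arms |
| Intracranial compliance | T1 initial data, T2 effect of MHM | assessed at T3; a pre-aspiration T2 is implied, not stated |
| Table 1 | no intervention marked at T1 | interventions marked at T2 and T3 |

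Four statements make T1 pre-maneuver. The later sentences under Fig. 2 depart from them.

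**Clock, in minutes from T0 = 0.** Inputs are 5 initial minutes, a T1 block of 10 minutes, T2 and T3 blocks of 5 minutes each, and an MHM of 10 minutes (all under Fig. 2). Aspiration is three passes of 15 s, with 100% oxygen for 30 s before and 60 s after (Experimental group section).

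- Moments: T1 at 5, MHM from 5 to 15, T2 at 15, then aspiration, then T3. T1 is untreated and T2 precedes aspiration.
- Blocks: T1 runs from 5 to 5 + 10 = 15. The 10-minute MHM fills it, so 10 of 10 one-minute averages in the experimental arm fall during the maneuver. T2 runs from 15 to 20 and contains aspiration.
- Share of the T2 block after aspiration, assuming that it starts at once and the passes are back to back: 30 s + 3 × 15 s = 75 s = 1.25 min. This leaves 5 − 1.25 = 3.75 min after the last pass, or 2.75 min after the further 60 s of oxygen.
- Control group wording placed on the same blocks: aspiration falls in 20 to 25. T2 then precedes it, and a T3 value could be recorded during it.

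**What this does to the comparisons.** Let d1 be the mean effect of the MHM on the waveform index while it runs, and d2 its effect at T2.

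- Difference between arms in the change from T1 to T2, with T1 before the MHM: d2 − 0 = d2.
- The same with T1 recorded during the MHM: d2 − d1. If the effect is sustained, d1 and d2 have the same sign and similar size, and the result moves toward zero. If the effect fades quickly, the result is still wrong but need not move toward zero.
- Difference between arms at T2 alone: d2, whatever window T1 uses.
- Difference at T2 when T2 includes aspiration, with responses sE and sC in the two arms: d2 + (sE − sC). If the responses are equal, the mean difference is unchanged, although each reading mixes two procedures. If they differ, which is what T3 is meant to examine, the MHM effect is no longer isolated. The article gives no basis for a direction.

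**The case against.** The strongest defence is that each T is the reading that opens the block named after it. T1 is taken, the MHM runs for 10 minutes, T2 is taken, aspiration follows, and then T3. This fits the Abstract, the Intracranial compliance section and most of the text under Fig. 2, and it is compatible with Table 1. The order of procedures, maneuver first and aspiration second, is the same throughout. Fig. 2 is not shown here and may draw the timeline clearly.

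Much of this stands: the intended design is fairly clear. It does not remove the conflict. No sentence says that readings are taken at the start of a block, and aspiration remains in T2 in one section and in T3 in another. A clear figure would still leave contradictory text.

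It is also fair that Statistical methods names a two-way repeated-measures ANOVA and between-group tests, but no change from T1. The T1 problem affects only analyses that use T1, such as the group-by-time comparison.

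A reader might infer more than the article supports:

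- **Aspiration timed differently in the two arms.** Under Fig. 2, both groups are aspirated in T2. The Control group section aspirates controls together with the experimental group and monitors both at the same moments. Each section times the arms alike.
- **A fixed share of the effect lost.** That would require a T2 − T1 change score and averaging over the whole block, and the article states neither.
- **Readings actually mis-timed.** The text shows only that they could be.

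**Conclusion.** The definitions of T1 and T2 conflict in the current text and need to be reconciled. The conflict itself is certain; its consequences are conditional. If the block wording governs extraction, all 10 T1 minutes in the experimental arm lie within the MHM. A T1-to-T2 group-by-time comparison is then biased toward no difference, provided the effect is sustained. A comparison at T2 alone escapes the T1 problem. It would still include the aspiration response in both arms, for about 3.75 of 5 minutes after the last pass under the timing assumption above. The size of the bias on the waveform indices cannot be derived from the article. If extraction follows the moment definitions, neither problem arises. The matter is worth settling because it concerns the baseline and the key reading of the primary outcome, and settling it is cheap.

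**What to change.** Reconcile the Abstract, the text under Fig. 2, the Control group section, the Intracranial compliance section and Table 1 to one timeline common to both arms. State which minutes supply each value:

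- T1: minutes before any ventilator change.
- T2: minutes after the maneuver, or the matching control monitoring, has ended and before aspiration.
- T3: minutes after aspiration.

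These are measurement windows tied to events. They do not change what is done to patients. Extract the stored sensor recordings to these windows by logged event time, with the person doing so masked to arm.

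The cost is a wording change and re-segmentation of recordings already held, with no new procedure. There are two limits. Re-extraction works only if event times were logged in both arms. Respiratory-mechanics readings rest on inspiratory pauses made at the time, so those already taken cannot be re-cut, and their actual timing should be reported.
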